#### Secondary research questions

We will also: 1) assess the effects on antibiotic consumption; 2) estimate the cost-effectiveness from the perspectives of the NHS, patients, and society; 3) compare the burden, severity and duration of abnormal peak flow and LRTI symptoms; 4) compare adverse events including any new symptoms or worsening of existing symptoms, re-consultations for a documented deterioration in illness and serious adverse events; 5) investigate if participants’ subjective or objective response to oral steroids is associated with a clinical diagnosis of asthma or COPD; and 6) assess participants’ satisfaction with treatment and intention to consult for future similar illnesses.

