#### Inclusion criteria

The following inclusion criteria must all apply:Aged 18 years or over;Consulting for an acute (≤28 days) cough as the main presenting symptom;In the past 24 hours, the patient has had at least one of the screening symptoms listed below (a-d), localising to the lower respiratory tract and suggestive of an acute LRTI:phlegm (sputum)chest painshortness of breathwheezePatient and practice have sufficient time for consent and randomisation into the trial by the end of the day of consultation, or the next working day as long as this is within 24 hours;Patient able and willing to give informed consent themselves;Patient able and willing to complete the daily symptom diary themselves;Patient able, willing and available to receive weekly telephone calls from the trial team.

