### Outcomes

#### How the outcome measures will be ascertained

The OSAC trial will use validated patient completed symptom diary methods [37] that have been used in a number of similar previous trials [2,5]. Participants will record in the diary the severity of the following symptoms: cough; phlegm; shortness of breath; sleep disturbance; feeling generally unwell; activity disturbance. A symptom score scale of 0 to 6 will be used (0 = no problem, 1 = very little problem, 2 = slight problem, 3 = moderately bad, 4 = bad, 5 = very bad, and 6 = as bad as it could be) which is shown to be sensitive to change and internally reliable [5]. For this trial, we will record all the above symptoms for up to 28 days (or until symptom resolution for two consecutive days) since LRTI duration has been previously shown to last 3 to 4 weeks [5]. Cough duration and severity will be measured for up to 8 weeks since effects on these may not be apparent for some time after using corticosteroids.

For this trial, participants will also record their peak expiratory flow in the morning and the evening for the duration of their illness up to 28 days, and measure their quality of life at weekly intervals (up to 4 weeks) using the EQ-5D-5L validated questionnaire [38], which has been shown to be moderately responsive in participants with acute cough/LRTI, and is a suitable measure for use in economic evaluation studies of this illness [39].

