#### Secondary outcome measures

Antibiotic consumption;Duration of corticosteroid tablet use;Total duration and severity of symptoms (cough; phlegm; shortness of breath; wheeze; blocked/runny nose; chest pain; fever; muscle aching; headache; sleep disturbance; feeling generally unwell; activity disturbance), until the severity of each is scored by the participant as ‘1’ or ‘very little problem, and abnormal peak flow (defined as a peak flow reading that is not within the range of values that would be expected according to a standard predictive algorithm based on gender, height and weight);Adverse events including re-consultation for a documented illness deterioration;Patient satisfaction with treatment and intention to use the same treatment if it were to be available in the future;Clinical diagnosis of asthma, COPD, whooping cough (pertussis), or lung cancer at 3 months;Quality of life (using the EQ-5D-5L);NHS treatment and investigation costs, out-of-pocket patient and family costs, and the cost to society of time off work.

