#### Analysis of secondary outcomes

The secondary outcomes listed above (see “Secondary outcome measures”) will be analysed using appropriate regression models and will adjust for the baseline measure of the outcome, where possible, and centre.

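### Abnormal peak flow is defined in both directions and without age, so high readings count as illness and a treatment effect on this secondary outcome would be diluted

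*Protocol article*

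**What the plan says.** The Secondary outcome measures section defines abnormal peak flow as "a peak flow reading that is not within the range of values that would be expected according to a standard predictive algorithm". The same sentence names the inputs: the algorithm is "based on gender, height and weight". No other section restricts abnormality to low readings, adds age to the inputs, or describes an analysis of peak flow as a continuous or percent-predicted value.

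On measurement, the section on how outcomes will be ascertained says that "participants will also record their peak expiratory flow in the morning and the evening for the duration of their illness up to 28 days". On use, the Secondary research questions plan to "compare the burden, severity and duration of abnormal peak flow and LRTI symptoms", so an abnormal reading is treated as a sign of illness alongside symptoms. On analysis, secondary outcomes "will be analysed using appropriate regression models and will adjust for the baseline measure of the outcome, where possible, and centre".

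The age criterion for entry is "Aged 18 years or over", with no upper limit stated there. The exclusion criteria refer to patients over 65 and over 80.

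**The concern.** The hypothesis runs in one direction. The rationale for corticosteroids rests on airway inflammation, bronchial hyper-responsiveness and reduced forced expiratory volume during respiratory infection, and the rationale for the design speaks of relieving bronchospasm. Narrowed airways lower peak flow; a reading above the expected range is not evidence of the illness being treated. A rule covering both tails therefore adds readings with no bearing on the hypothesis to those that have one.

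This has two consequences. A participant whose usual flow lies above the range would be scored abnormal for as long as they keep recording, which is the duration of their illness and at most 28 days. In addition, the misclassification is not necessarily equal between arms: if treatment raises flow, the share of readings above the upper limit grows in the active arm while the share below the lower limit shrinks. The two movements partly cancel in a single count.

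Leaving age out of the algorithm is a lesser, separate matter. If peak flow varies with age in adults, a range that ignores age is badly placed for some participants at either end of a wide age span.

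**Working it through.** The protocol article gives no peak flow mean, SD, range width or expected effect, so there is no figure to reproduce. The check has a textual part and an illustrative part.

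**Text**

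1. Direction: the definition covers any reading outside the range, with no mention of the lower limit. Both tails count.
2. Inputs: gender, height and weight are listed; age is not. Age is available, because it is an entry criterion and a planned subgroup factor.
3. Purpose: burden, severity and duration of abnormal peak flow are compared between arms together with symptoms, so abnormal stands for ill.

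**Illustration (all values assumed)**

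Express a reading in reference SD units from its predicted value and take it as normal with mean m and SD 1. Let the range be ±L and let treatment raise the mean by d. With Φ the standard normal distribution function:

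- low readings: Φ(−L − m)
- high readings: 1 − Φ(L − m)
- abnormal under the stated rule: the sum of the two

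For the active arm, replace m by m + d.

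With L = 1.96, d = 0.3 and control mean m = −0.5 (active mean −0.2):

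- low: Φ(−1.46) = 7.2% to Φ(−1.76) = 3.9%, ratio 0.54
- high: 1 − Φ(2.46) = 0.7% to 1 − Φ(2.16) = 1.5%
- abnormal as stated: 7.9% to 5.5%, ratio 0.69

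The range over other assumed values, with d = 0.3 throughout (ratios from unrounded values):

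| Limits | Control mean | Low readings only | Ratio | Rule as stated | Ratio |
|---|---|---|---|---|---|
| ±1.96 | −1 | 16.9% to 10.4% | 0.62 | 17.0% to 10.8% | 0.63 |
| ±1.96 | −0.5 | 7.2% to 3.9% | 0.54 | 7.9% to 5.5% | 0.69 |
| ±1.96 | 0 | 2.5% to 1.2% | 0.48 | 5.0% to 6.0% | 1.21 |
| ±1.645 | −1 | 25.9% to 17.2% | 0.66 | 26.4% to 18.2% | 0.69 |
| ±1.645 | −0.5 | 12.6% to 7.4% | 0.59 | 14.2% to 10.7% | 0.75 |
| ±1.645 | 0 | 5.0% to 2.6% | 0.52 | 10.0% to 11.5% | 1.15 |

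**When the direction reverses**

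With symmetric limits, the two-tailed proportion depends only on |m| and increases with it. Treatment therefore raises the abnormal proportion when |m + d| > |m|, that is, when m > −d/2. For d = 0.3 the control mean must lie above −0.15 SD. Below that point the stated rule moves in the right direction but by less; by m = −1 the two rules nearly agree.

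These are proportions of single readings. The outcome also concerns duration, for which the article gives nothing to calculate from.

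**The case against.** The best defence is that the context makes the intention clear. Abnormal peak flow sits in the same item as symptom duration and severity, so the authors very probably meant low readings, and an article may leave the choice of algorithm and cut-off to a fuller document. That holds for the name of the equation and the width of the range. It does not dispose of the point, because the article does not leave the direction or the inputs open: it prints a rule, and an analyst who followed it would code high readings as abnormal.

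A reader might infer that a real benefit would show up as harm. The documents do not support that as the expected result. Reversal needs a group whose mean is close to or above predicted, whereas the Background reports significant reductions in forced expiratory volume during respiratory infection in people with and without asthma. That is a different measure from peak flow, but it points to a mean below predicted, where the effect is dilution. The exclusion of active asthma and chronic lung disease, and recording that continues as the illness resolves, make a mean near predicted possible for some readings, so reversal cannot be ruled out either.

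A reader might also take peak flow to be the trial's only objective measure of response. That is too strong. It is measured and recorded by the participants themselves, and the primary care notes review supplies contacts, prescriptions, referrals and diagnoses.

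On age, the objection largely stands. The article does not say that peak flow varies with age; that is general knowledge. Randomisation should balance age between arms, so its omission mainly adds noise and gives no reason to expect bias.

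**Conclusion.** The point holds as a minor one. The printed definition counts readings above the expected range as illness and builds that range without age, and nothing elsewhere in the article corrects either feature. The likely consequence is a diluted comparison of abnormal peak flow: in the illustration at 0.5 SD below predicted, a ratio of 0.54 for low readings becomes 0.69 with limits at ±1.96, and 0.59 becomes 0.75 with limits at ±1.645. Dilution is negligible if participants start about 1 SD below predicted.

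These sizes rest on assumed normality, symmetric limits, a 0.3 SD treatment effect and assumed starting means; none comes from the article. Only one component of a secondary outcome is affected. The primary outcomes and the sample size do not depend on it.

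**What to change.** Reword the definition so that a peak flow reading is abnormal when it falls below the lower limit of the expected range from a named reference equation that includes age as well as sex and height. Keep the planned adjustment for the baseline measure, where possible, and centre.

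The cost is one phrase in the outcome definition and the re-derivation of one variable. Age, sex, height and the diary readings are already part of the trial's data, so nothing new has to be collected. The article reports recruitment as complete and withholds the code-break until the primary analysis is done; if that point has not passed, the derivation can be settled while the team is still blinded.

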### Sample size calculation

Since the distributions of both primary outcome variables (the duration of moderately bad or worse cough and the mean severity score of all its associated symptoms on days 2 to 4 post-randomisation) will be positively skewed, sample size calculations are based on the log-normal distribution.

The mean (standard deviation (SD)) duration of bad or moderately worse cough was taken from a previous study examining the effectiveness of prescribed antibiotics for acute LRTI [5] and estimated as 5.8 (4.1) days. The mean (SD) symptom severity score between days 2 and 4 taken from the same trial was estimated as 2.3 (1.1). Using standard formulae for the mean and standard deviation of a log-normal distribution, this corresponds to 1.555 (SD 0.637) log days (or geometric mean of 4.74 days) for the cough duration outcome and 0.73 (SD 0.454) on the log scale (or geometric mean of 2.08) for the symptom severity outcome.

To account for testing multiple primary outcomes a lower alpha was specified for the symptom severity outcome to ensure that the overall alpha for the two primary outcomes remains close to 5%. Moderately bad or worse cough has been shown to resolve within 7 days for 50% of patients, 14 days for 75% and 4 weeks for 90% of patients [5]. Therefore, since duration of cough lasts significantly longer than the period during which severity of symptoms are measured (days 2 to 4) and is capturing an element of the illness severity, duration of moderately bad or worse cough might be viewed as the slightly more clinically important outcome. For this reason alpha remained at 5% for duration of cough and was reduced to 0.1% for symptom severity.

Sample size was calculated based on a 20% reduction in the duration of cough, corresponding to a geometric mean in the active treatment group of 3.79 days (mean 1.333 log days). Allowing (conservatively) for 20% attrition, 218 participants will need to be randomised per arm to retain 174 at follow-up and achieve 90% power with a two-sided alpha of 0.05. Hence a total sample size of 436 is required.

For the symptom severity outcome, a final achieved sample size of 174 participants in each arm will provide 89% power to detect a reduction in symptom severity score between days 2 and 4 of 20%, corresponding to a geometric mean of 1.66 units in the active group (mean 0.51 log units) with a two-sided alpha of 0.001.

The trial team will make all efforts to recruit the 436 participants. If recruitment is slower than anticipated, recruitment will be extended until at least 163 have been recruited to each arm (326 in total). Assuming 20% attrition, this would provide the study with 80% power for both primary outcomes. All attempts will be made to ensure that attrition remains below 20% but if this is not feasible recruitment will be extended further if possible.

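### The mean (SD) behind the 90% power for cough duration cannot be true together with the recovery percentiles quoted from the same source; on those percentiles power is about 50%

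*Protocol article*

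**What the plan says.** All the figures are in the protocol article, section *Sample size calculation*.

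- The section says that "sample size calculations are based on the log-normal distribution". For duration of moderately bad or worse cough, the mean (SD) comes from an earlier antibiotic trial in acute LRTI, reference [5], and is "estimated as 5.8 (4.1) days". This is converted to a log-scale mean of 1.555 and SD of 0.637, a geometric mean of 4.74 days.
- The target is a 20% reduction, to a geometric mean of 3.79 days (log mean 1.333). With 20% attrition, 218 randomised and 174 retained per arm are said to "achieve 90% power with a two-sided alpha of 0.05".
- Between these two statements, in the paragraph that divides alpha, the section cites reference [5] again for the same symptom threshold. Moderately bad or worse cough is "shown to resolve within 7 days for 50% of patients, 14 days for 75% and 4 weeks for 90% of patients". This supports the argument that duration is the more important primary outcome and should keep the 5% alpha.

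The text after that section adds a fallback of 163 recruited per arm, said to give 80% power for both primary outcomes. It rests on the same log SD.

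**The concern.** One section gives two descriptions of the same quantity from the same reference. Short durations with modest spread set the sample size. Long durations with a heavy tail justify the alpha split. The log SD drives the calculation, because the required number grows with its square, so it matters which description is right.

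Duration is the outcome the protocol ranks as slightly more important. *Rationale for the trial design* also says that, if no effect is found, further research on lower doses is unlikely to be warranted. That reading of a null result leans on the stated power. If power is nearer one half, a true 20% reduction would be missed about as often as it is found.

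**Working it through.** **1. The plan's own figure.** Inputs: mean 5.8, SD 4.1, 20% reduction, two-sided alpha 0.05, power 90%, attrition 20%.

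- σ = √ln(1 + (4.1/5.8)²) = 0.637; μ = ln 5.8 − σ²/2 = 1.555; geometric mean e^1.555 = 4.74 days.
- n per arm = 2σ²(1.960 + 1.282)²/δ². With δ = 1.555 − 1.333 = 0.222 this gives 173.0, rounded up to 174. With δ = −ln 0.8 = 0.2231 it gives 172.
- 174/0.8 = 217.5, rounded up to 218 per arm, 436 in total.
- Power = Φ(δ/(σ√(2/n)) − 1.960), with δ = 0.2231: 90.4% at n = 174, and 80.6% at n = 130 (163 × 0.8).

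The stated numbers reproduce.

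**2. Can both descriptions hold, whatever the distribution?** The percentiles leave 50% of patients beyond 7 days, 25% beyond 14 and 10% beyond 28. In bands, 25% lie between 7 and 14 days, 15% between 14 and 28, and 10% above 28.

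- *Smallest mean.* Put the first half at zero and everyone else at the bottom of their band: 0.25×7 + 0.15×14 + 0.10×28 = 6.65 days. This exceeds 5.8. Capping every duration at 21 days still gives 0.25×7 + 0.15×14 + 0.10×21 = 5.95.
- *Smallest SD.* Pull everyone as close to the mean as their band allows: half at 7, 25% at the mean, 15% at 14, 10% at 28. The mean is then 11.2, and the variance is 0.50×(4.2)² + 0.15×(2.8)² + 0.10×(16.8)² = 8.82 + 1.18 + 28.22 = 38.22. The SD is 6.18 days, above 4.1.
- *Cantelli's inequality* as a cross-check. A mean of 5.8 and SD of 4.1 allow at most 4.1²/(4.1² + 8.2²) = 20% beyond 14 days, where 25% is needed. They allow at most 4.1²/(4.1² + 22.2²) = 3.3% beyond 28 days, where 10% is needed.

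All three checks exclude the pair.

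**3. The size of the gap under the planning log-normal (1.555, 0.637).**

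| | Planning log-normal | Quoted from reference [5] |
|---|---|---|
| Resolved by day 7 | 73.0% | 50% |
| Resolved by day 14 | 95.6% | 75% |
| Resolved by day 28 | 99.7% | 90% |
| Median, 75th, 90th percentile (days) | 4.7, 7.3, 10.7 | 7, 14, 28 |

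**4. Log SD implied by the percentiles, keeping the log-normal.**

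- From the 50th and 75th: ln(14/7)/0.6745 = 1.028.
- From the 50th and 90th: ln(28/7)/1.2816 = 1.082.

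**5. Power on those values (δ = 0.2231, two-sided alpha 0.05).**

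| Log SD | Power, 174 per arm | Power, 130 per arm | Analysed per arm for 90% | Randomised per arm at 20% attrition |
|---|---|---|---|---|
| 0.637 | 90.4% | 80.6% | 172 | 215 |
| 1.028 | 52.6% | 41.7% | 446 | 558 |
| 1.082 | 48.6% | 38.3% | 494 | 618 |

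These use the normal approximation. The t distribution lowers them slightly, to 52.4% and 48.4% at 174 per arm. Using only the 75th and 90th percentiles gives a log SD of 1.142 and power of 44.5%.

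**6. Reduction detectable with 90% power at 174 per arm.** 1 − exp(−3.2415 × σ × √(2/174)) = 30.0% at σ = 1.028 and 31.3% at σ = 1.082.

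**7. Closer to the planned analysis.** *Analysis of primary outcomes* specifies a Cox model with censoring at 28 days. A simulated log-rank test with that censoring, whole-day durations and 2,000 trials per setting gave power of about 85% on the planning log-normal. On the percentile-based values (log SD 1.028 and 1.082) it gave about 45% and 41%.

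**The case against.** Five points can be made for the plan.

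- *The percentiles are not an input.* They support the alpha split only, and the calculation itself has no slip. This is true. But the same section presents them as facts about the same outcome from the same source, so they bear directly on whether the input is right.
- *The percentiles may be the wrong set.* *Background* says, from the same reference, that the worst symptoms can last up to a week, which sits more easily with the planning figures. If the percentile sentence describes another endpoint, population or time origin, the 90% stands. This cannot be excluded. That wording is loose, however, and no such difference is stated. Moving the time origin by a constant would lower the mean but not the minimum SD of 6.18. The plan to telephone patients up to day 56, partly to find the last day of moderately bad cough, fits the longer durations better. Of 348 analysed, about 1 (0.26%) would still be at that level after day 28 under the planning log-normal, against about 35 (10%) under the percentiles.
- *The 50% figure depends on a model.* This stands. Only the incompatibility is distribution-free; taken alone, the three percentiles force a log SD of no more than about 0.43, in a degenerate case. Log-normality is nevertheless the protocol's own assumption.
- *The power figures ignore censoring and the Cox model.* This also stands, but the censored check shows a gap of similar size.
- *Recruitment is complete, and a null result will be judged by its confidence interval.* This is fair: a narrow enough interval could still exclude a 20% reduction. With the larger SD, though, such an interval is less likely, and the article would still carry a power claim that its own figures dispute.

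**Conclusion.** The section is wrong as written. A mean (SD) of 5.8 (4.1) days and the quoted percentiles cannot describe the same duration, under any distribution. At least one set is wrong, or refers to something other than what the text says.

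If the percentiles are right, and the protocol's log-normal model and 20% effect are kept, power for cough duration is about 48–53% at 174 per arm rather than 90%. At the fallback of about 130 per arm it is about 38–42% rather than 80%. The reduction detectable with 90% power is about 30–31%. If the mean and SD are right, the stated power stands. For a log SD anywhere from 0.64 to 1.08, power runs from 90% down to 48%.

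The incompatibility assumes only that both sets share an outcome and a time origin, as the text presents them. The power figures also assume log-normality and a comparison of log means without censoring.

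**What to change.** 1. Check both sets of figures against reference [5]. Correct whichever is wrong, or state the difference in origin, population or definition that explains them.
2. Restate power for cough duration over log SD 0.64 to 1.08, at 174 per arm and at the fallback size. Give the reduction detectable with 90% power at the achieved sample size.
3. If the percentile sentence turns out to be the error, review the alpha-split argument that leans on it.
4. Use the restated range, with the confidence interval, when interpreting a null result. Qualify accordingly the statement in *Rationale for the trial design* about further lower-dose research.

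The cost is re-reading one source and changing a few lines of text. No patients are added. The stated power may become less favourable.

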## Discussion

This paper describes a placebo-controlled, randomised multi-centre superiority trial that will establish the clinical and cost effectiveness of a commonly used treatment (corticosteroids) for an entirely novel indication and one of the commonest clinical problems managed in primary care: acute LRTI. The trial will recruit between 326 and 436 non-asthmatic adult patients presenting to primary care with an acute cough of less than 28 days duration and at least one other lower respiratory tract symptom or physical examination finding. Eligible, consented patients will be randomised to receive a 5-day course of either the active treatment (2 × 20 mg prednisolone daily) or matched placebo, and asked to complete a symptom diary for at least 7 and up to 28 days, depending on the duration of their illness. Participants will be telephoned weekly for 4 weeks, or until their cough resolves, up to a maximum of 8 weeks from recruitment.

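### The fallback size of 326 does not give 80% power for both primary outcomes: symptom severity, tested at alpha 0.1%, has only about 74–75%

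*Protocol article*

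**What the plan says.** The Sample size calculation section works on the log scale and assumes a 20% reduction for both primary outcomes. The alpha is split unequally: "alpha remained at 5% for duration of cough and was reduced to 0.1% for symptom severity".

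For cough duration, 218 are randomised per arm "to retain 174 at follow-up and achieve 90% power with a two-sided alpha of 0.05". For symptom severity, the same 174 per arm are said to give 89% power at two-sided alpha 0.001.

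The section then sets a floor for slow recruitment of at least 163 per arm, 326 in total, and states: "Assuming 20% attrition, this would provide the study with 80% power for both primary outcomes". It gives no different alpha, effect size or SD for this floor. The Discussion repeats the floor as the lower end of the planned range: "The trial will recruit between 326 and 436 non-asthmatic adult patients".

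**The concern.** At the full size the two outcomes have almost equal power (90% and 89%), but at very different alphas. Power at alpha 0.001 falls faster as the sample shrinks than power at alpha 0.05. Two outcomes that start level at 174 per arm should therefore not both land on 80% at 130 per arm.

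The 80% figure is the stated justification for accepting 326 as the minimum. Symptom severity is one of two primary outcomes. The section on the rationale for the trial design says that finding no treatment effect would make further research at lower doses unlikely to be warranted. The chance of missing a true 20% reduction in severity therefore bears on how a null result is read, and at the floor that chance is larger than the protocol tells the reader.

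**Working it through.** **Inputs** (all from Sample size calculation)

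- Cough duration: "this corresponds to 1.555 (SD 0.637) log days (or geometric mean of 4.74 days) for the cough duration outcome"; active-arm log mean 1.333; two-sided alpha 0.05.
- Symptom severity: "0.73 (SD 0.454) on the log scale (or geometric mean of 2.08) for the symptom severity outcome"; active-arm log mean 0.51; two-sided alpha 0.001.
- Effect for both: a 20% reduction, so d = −ln(0.8) = 0.2231. The printed log means give 1.555 − 1.333 = 0.222 and 0.73 − 0.51 = 0.22.
- Fallback: 163 × 0.8 = 130.4, taken as 130 analysed per arm.

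**Formula.** Two-sample comparison of means, normal approximation: power = Φ( d / (SD × √(2/n)) − z ), with z = 1.960 for alpha 0.05 and z = 3.291 for alpha 0.001. Each result was cross-checked with the noncentral t.

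**Step 1: reproduce the full-size figures (n = 174 per arm)**

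- Duration: 0.2231 / (0.637 × √(2/174)) = 3.27; 3.27 − 1.96 = 1.31; power 90.5% (t: 90.3%). Stated: 90%.
- Severity: 0.2231 / (0.454 × √(2/174)) = 4.58; 4.58 − 3.29 = 1.29; power 90.2% (t: 89.6%). With the printed difference of 0.22: 89.1% (t: 88.4%). Stated: 89%.

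The method matches the protocol's own.

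**Step 2: apply it to the fallback (n = 130 per arm)**

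- Duration: 0.2231 / (0.637 × √(2/130)) = 2.82; 2.82 − 1.96 = 0.86; power 80.6% (t: 80.3%). The stated 80% is right.
- Severity: 0.2231 / (0.454 × √(2/130)) = 3.96; 3.96 − 3.29 = 0.67; power 74.9% (t: 73.6%). The stated 80% is not reproduced.

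**Step 3: sensitivity of severity power to rounding**

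| Input for d | n per arm | Normal | Noncentral t |
|---|---|---|---|
| −ln(0.8) | 130 | 74.9% | 73.6% |
| −ln(0.8) | 131 | 75.4% | 74.1% |
| Printed log means (0.22) | 130 | 73.1% | 71.8% |
| Ratio of printed geometric means (2.08/1.66) | 130 | 76.3% | 75.0% |

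The second row shows that rounding 130.4 up does not help.

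**Step 4: other readings**

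- One-sided alpha 0.001 gives 80.9% at 130 per arm, but it would give 93% at 174, not 89%, and the text says two-sided.
- Ignoring attrition (163 analysed) gives about 87%, but the sentence assumes 20% attrition.
- Raw-scale means and SD give 53% at 130.
- The two-sided alpha would have to be about 0.0018 to give 80% at 130.

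**Step 5: where 163 probably comes from.** With the printed log means for duration (difference 0.222), normal-approximation power is 79.9% at 129 per arm and 80.2% at 130. The smallest adequate number is therefore 130, and 130/0.8 = 162.5, rounded up to 163. The same inputs give 174 for 90% power. The floor is thus what cough duration alone would produce. This is an inference; the protocol does not say how 163 was derived.

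**Step 6: size needed for 80% severity power.** n = 2 × (3.291 + 0.842)² × 0.454² / 0.2231², which gives 142 analysed per arm. Then 142/0.8 = 177.5, so 178 randomised per arm and 356 in total. The noncentral t gives 145 analysed; 145/0.8 = 181.25, so 182 per arm and 364 in total.

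**The case against.** The arithmetic is hard to dispute; the case on the other side is about weight.

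- **It is a contingency figure.** The design target is 436, with correct powers, and 326 is a minimum for slow recruitment. No test, alpha, model or data collection depends on the sentence. This stands, and it limits the consequence.
- **The more important outcome is right.** The protocol treats cough duration as slightly more important clinically, and its 80% is correct. This also stands, but the sentence makes the claim for both outcomes.
- **Attrition may be lower than 20%.** The protocol calls 20% conservative, and severity is measured only on days 2 to 4, with a telephone call within the first 2 days. Severity power would reach 80% if attrition were no more than about 13% (1 − 142/163, normal) or 11% (1 − 145/163, t). That is possible, but the sentence states its power on the assumption of 20%.
- **The harm is conditional.** The Trial status section says recruitment ended in October 2014 but gives no final number, so nothing shows that the trial stopped near 326. Effect estimates are to be reported with 95% confidence intervals, which would show the precision of a null result directly. This is fair: any misreading of a null severity result is a risk, not a certainty.

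**Conclusion.** The statement is wrong as written. At the declared minimum size with 20% attrition, power is about 80% for cough duration and about 74–75% for symptom severity. Depending on which printed inputs are used and on normal or t, the severity figure lies between about 72% and 76%; no version consistent with the text reaches 80%. The shortfall is about 5 to 6 points on the main calculation, which puts the type II error at about 25–26% instead of 20%.

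This rests on the protocol's own assumptions: log-normal outcomes, a 20% reduction, log SD 0.454, two-sided alpha 0.001 and 130 analysed per arm. The full-size calculation for 436 is sound.

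**What to change.** Replace the sentence with one that gives the two powers separately. For example: with 163 randomised per arm and 20% attrition (about 130 analysed per arm), power is about 80% for cough duration at two-sided alpha 0.05 and about 74% for symptom severity at two-sided alpha 0.001. Where the Discussion gives 326 as the lower bound, it should be read with that qualification.

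This costs one sentence and a slightly less favourable figure; it needs no extra patients and no change to the analysis. The alternative, if 80% is required for both outcomes, is to raise the floor to 356 (normal approximation) or 364 (noncentral t) in total, which is 30 to 38 more than 326. That choice is the sponsor's. As recruitment is reported complete, correcting the statement is the practical course.
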